## Materials and methods

### Study hypothesis and primary outcome

The primary hypothesis of this study is that the SGLT-2 inhibitor is superior to other oral hypoglycemic medications for rhythm control in patients with AF and DM, diagnosed within the prior year. A step-up treatment will be carried out when the participant’s AF recurs. The recurrence rate of AF will be investigated after performing stepwise rhythm control therapies including anti-arrhythmic drugs (AAD) and ablation. AF is defined as per the 2019 AHA/ACC/HRS Guideline, i.e., irregular R–R intervals (when atrioventricular conduction is present), absence of distinct repeating P waves, and irregular atrial activity [20]. It is checked by 24-h Holter ECG every 3 months and is considered significant when it lasts for > 30 s [21].

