### Secondary outcomes

Secondary outcomes are listed in Table 1. AF-free survival will be compared between the two groups as the first of the secondary outcome, analyzed using the Kaplan–Meier method, and documented on curve. AF burden at 3-month follow-up visit, 12-month follow-up visit in those who did not step up and used AAD only for rhythm control, immediately before trying ablation, and at 12-month follow-up visit in those who stepped up and underwent ablation in both the SGLT-2 inhibitor group and the control group will be compared. AF burden is defined as the atrial fibrillation time percentage documented on 24-h Holter ECG [22]. Ablation rate, which is the percentage of patients undergoing ablation, within a year will also be compared between the two groups to identify the efficacy of symptom and rhythm control using SGLT-2 inhibitors. Sinus rhythm is considered stable when either a standard ECG or a 24-h Holter ECG showed no episode of clinically relevant arrhythmia, including AF, at the time of check-up [23]. The proportion of participants with stable sinus rhythm in all participants, regardless of with or without ablation, is compared between the two groups at baseline, 6-, and 12-month follow-up visits.

**Table 1 pone.0280359.t001:** Secondary outcomes.

• Rhythm control • AF-free survival • AF burden at • 3-month F/U visit, 12-month F/U visit in those who did not step up to session 2 • Immediately before trying ablation, 12-month F/U visit in those who stepped up to session 2 • Percentage of patients undergoing ablation within a year • Sinus rhythm maintenance* • Diameter of LA • NT-proBNP • Symptom score (EHRA score) • Quality of life (EQ-5D, SF-12)

*Defined as the absence of clinically relevant arrhythmia (e.g., AF, AFL, sustained VT, and VF).

AF, atrial fibrillation; LA, left atrium; F/U, follow up; NT-proBNP, N-terminal pro-B-type natriuretic peptide; EHRA, European Heart Rhythm Association; EQ-5D, EuroQol-5 Dimension; SF-12, Short Form-12 Health Survey Questionnaire; AFL, atrial flutter; VT, ventricular tachycardia; VF, ventricular fibrillation.

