**Fig 2 pone.0280359.g002:**
[figure not shown]
Flow chart of the trial. Brief flow of the BEYOND trial described as a schematic diagram. Patients who enroll this trial will be randomly administrated SGLT-2 inhibitor or other DM medication while applying stepwise rhythm control strategy for AF.

Patients diagnosed with AF within a year, who have never undergone any ablation treatment, newly diagnosed with DM, and with ages between 18 and 80 years will be selected as the study participants. They will be enrolled in 7 tertiary medical centers from the Division of Cardiology and the Division of Endocrinology. As patients diagnosed with AF also tend to check for DM to calculate the CHAD2-VASc score, those who have been diagnosed as AF in the prior year and newly diagnosed with DM in the follow-up can be recruited for the trial in the Division of Cardiology. To identify patients for enrollment in the Division of Endocrinology, every patient newly diagnosed with DM during the enrollment period will be asked for 12-lead ECG and 24-h Holter ECG; those with AF > 10 s in 12-lead ECG or >30 s in 24-h Holter ECG can be recruited for the trial. All participants must meet the required inclusion (Table 3) and exclusion criteria (Table 4) at the point of randomization. The participants should otherwise be healthy and use only oral hypoglycemic agents, not subcutaneous agents, for glycemic control.

**Table 3 pone.0280359.t003:** Inclusion criteria.

• At least one episode of AF* that is documented during the prior year by any kind of ECG recording. • Type 2 DM was diagnosed (HbA1c > 6.5%) and the patient was using oral hypoglycemic agents only for glycemic control. • At least 18 years old, but not older than 80 years. • Normal ECG parameters, measured in sinus rhythm (QRS width ≤ 120 ms, QTc interval < 440 ms, and PQ interval ≤ 210 ms in a 12-lead ECG). • Be able and willing to give informed consent.

*AF episode must last longer than 30 s on single ECG, 10 s on 12-lead ECG or 24-h Holter ECG.

AF, atrial fibrillation; DM, diabetes mellitus; ECG, electrocardiogram.

**Table 4 pone.0280359.t004:** Exclusion criteria.

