### Follow-up and detection of AF recurrence

After their recruitment, the participants will receive baseline and evaluation studies under scrutiny, which include history taking, physical examination, blood sampling, urine sampling, 12-lead ECG, 24-h Holter ECG, TTE, EHRA, EQ-5D, and SF-12. The follow-up schedule will begin with the prescription of oral hypoglycemic agents (Table 5). During each intervention, the following steps were conducted: (1) history taking for the review of AF and DM status, adverse events, and other specific illnesses on every visit; (2) physical examination to evaluate any DM complication, AF, NYHA score, neurologic exam, systolic and diastolic blood pressure; (3) blood sampling for CBC, BUN/Cr, electrolyte, coagulation profile, HbA1c, fasting glucose, AST/ALT, lipid battery, and NT-proBNP; (4) urine sampling for dip stick urinalysis with microscopy and measuring proteinuria (especially for albuminuria); and (5) TTE to measure the LA size and left ventricular ejection fraction (LVEF). Any other additive assessing procedure may be conducted and recorded during the clinical course of the patients.

**Table 5 pone.0280359.t005:** Data-collection requirements.

Investigation	Baseline	3M	6M	9M	12M
Inclusion/Exclusion criteria	X				
Medical History	X	X	X	X	X
Physical Examination	X	X	X	X	X
12-lead ECG	X	X	X	X	X
24-h Holter ECG*	X	X	X	X	X
Blood, Urine sample	X				X
Transthoracic Echocardiography (TTE)	X				X
NT-proBNP	X				X
EHRA Score	X	X	X	X	X
EQ-5D, SF-12	X				X
Adverse Events History**		X	X	X	X

*Patients with an ablation (RFA or 4PVI) will be monitored every 3 months that point on for an additional year.

**To evaluate adverse events, any suitable diagnostic investigation can be performed.

Abbreviations. ECG, electrocardiogram; NT-proBNP, N-terminal pro-B-type natriuretic peptide; EHRA, European Heart Rhythm Association; EQ-5D, EuroQol-5 Dimension; SF-12, Short Form-12 Health Survey Questionnaire.

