### Statistical plan, sample size, and power determination

In this study, 716 patients will be enrolled from 7 tertiary medical centers. The sample size was determined based on the primary outcome, i.e., the SGLT-2 inhibitors should show 40% reduction in AF after a year of treatment [32] and 50% of AAD users should step up to the ablation therapy [33,34]. Assuming 10% follow-up loss, the sample size of 716 patients (358 in each group) is expected to achieve 80% power and an alpha-level of 5% to detect the difference. The study is powered to demonstrate the superior additive effect of SGLT-2 inhibitors over other hypoglycemic agents using the Chi square method. AF recurrence rate and ratio of sinus rhythm on 24-h holter EKG will be analyzed using Chi square test, and left atrial size, NT-pro BNP and quality of life (AFEQT) score on 12-month final follow-up will be analyzed by student t-test. Disease-free survival and overall survival during the follow-up period will be calculated using Kaplan-Meier method. Mono-variable and multi-variable cox regression analysis will be used to calculate hazard ratio of SGLT-2 group.

To reduce the selection bias, all subjects will be randomized to allocate the hypoglycemic agents according to random number table. Missing data is planned to be controlled using multiple imputation.

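### The stable sinus rhythm outcome needs only one clean recording, which contradicts the Table 1 footnote and the Holter-based analysis, and lets a clean visit ECG override AF on Holter

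*Protocol article*

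**What the plan says.** The protocol article describes this outcome in three places.

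- **Secondary outcomes, text:** "Sinus rhythm is considered stable when either a standard ECG or a 24-h Holter ECG showed no episode of clinically relevant arrhythmia". The proportion meeting this "is compared between the two groups at baseline, 6-, and 12-month follow-up visits".
- **Secondary outcomes, Table 1 footnote to sinus rhythm maintenance:** "Defined as the absence of clinically relevant arrhythmia (e.g., AF, AFL, sustained VT, and VF". No recording is named.
- **Statistical plan, sample size, and power determination:** "AF recurrence rate and ratio of sinus rhythm on 24-h holter EKG will be analyzed using Chi square test". Only the Holter is named.

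Two further statements bear on it. For AF in the primary outcome, Study hypothesis and primary outcome says: "It is checked by 24-h Holter ECG every 3 months and is considered significant when it lasts for > 30 s". Table 5, under Follow-up and detection of AF recurrence, marks both the 12-lead ECG and the 24-h Holter at baseline and at 3, 6, 9 and 12 months.

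**The concern.** As worded, the rule is a logical OR on clean recordings: one is enough. Because both recordings are scheduled at each visit where the outcome is compared, they can conflict, and the article does not say that the Holter prevails. A 12-lead ECG covers far less time than a 24-h Holter and will miss AF that comes and goes. The rule therefore lets the less sensitive recording cancel the more sensitive one.

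Two things are at stake. First, at one and the same visit a patient can be a recurrence for the primary outcome and a success here. Second, counting such patients as successes raises the sinus-rhythm proportion in both arms and can shrink the difference between them.

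**Working it through.** No figure in the article depends on this definition, so there is none to reproduce. The check has two parts.

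**1. One patient under each statement.** Take a visit with more than 30 s of AF on Holter and a clean 12-lead ECG.

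| Statement | Classification |
|---|---|
| Secondary outcomes, text (either recording clean) | stable sinus rhythm |
| Table 1 footnote (absence of arrhythmia) | not sinus rhythm |
| Statistical plan (sinus rhythm on Holter) | not sinus rhythm |
| Primary outcome (Holter, more than 30 s) | AF recurrence |

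The first row stands alone against the other three.

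The baseline comparison is also weakened. Table 3 requires "Normal ECG parameters, measured in sinus rhythm". If that eligibility ECG serves as the baseline ECG, nearly every participant is stable at baseline under the either-clean rule, whatever the Holter shows.

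**2. Size of the dilution (illustration).**

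Inputs from the article: 358 per group and 10% follow-up loss, so 358 × 0.9 = 322.2, taken as 322 evaluable per arm; alpha 5%; a 40% reduction in AF.

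Assumptions, none of them given in the article:
- alpha is two-sided;
- the control proportion with AF on Holter at the visit is 50% or 30%, and the 40% reduction is applied to it (0.50 × 0.6 = 0.30; 0.30 × 0.6 = 0.18);
- AF on the visit ECG occurs only in patients who also have AF on Holter, with probability s, equal in both arms.

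Let p_C and p_T be the control and SGLT-2 proportions with AF on Holter. Under a Holter rule, sinus rhythm is 1 − p in each arm and the difference is p_C − p_T. Under the either-clean rule a patient fails only if both recordings show AF, so sinus rhythm is 1 − s·p and the difference is s·(p_C − p_T).

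Power = Φ[(d − 1.96·SE0)/SE1], where d is the difference, SE0 the pooled and SE1 the unpooled standard error of two proportions with 322 per arm.

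Example, p_C = 0.50, p_T = 0.30, s = 0.3: sinus rhythm is 1 − 0.15 = 0.85 versus 1 − 0.09 = 0.91, so d = 0.06. SE0 = √(2 × 0.88 × 0.12/322) = 0.0256. SE1 = √(0.85 × 0.15/322 + 0.91 × 0.09/322) = 0.0255. Power = Φ(0.384) = 65%.

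| Rule | Holter AF 50% vs 30%: sinus rhythm | Power | Holter AF 30% vs 18%: sinus rhythm | Power |
|---|---|---|---|---|
| Holter (same as s = 1) | 50% vs 70% | >99% | 70% vs 82% | 95% |
| Either clean, s = 0.1 | 95% vs 97% | 25% | 97% vs 98.2% | 17% |
| Either clean, s = 0.3 | 85% vs 91% | 65% | 91% vs 94.6% | 42% |
| Either clean, s = 0.5 | 75% vs 85% | 89% | 85% vs 91% | 65% |
| Either clean, s = 0.7 | 65% vs 79% | 98% | 79% vs 87.4% | 82% |

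Roughly, s equals the share of the day spent in AF, because a short ECG at an arbitrary time is clean with probability about one minus that share. Low-burden paroxysmal AF gives a small s; persistent AF gives s near 1. If s differs between arms, the difference becomes s_C·p_C − s_T·p_T, and the outcome mixes recurrence with burden.

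**The case against.** The best defence is that this is loose wording and not a chosen scoring rule. The sentence may have been meant as neither recording showing an episode, or as whichever recording was made. The Table 1 footnote and the statistical section both favour a stricter reading, and if the analysis follows the statistical section the misclassification does not occur. The sentence also cites a published source that is not at hand. All of this is plausible as to intent. It does not remove the point: the text states neither looser reading, and the statistical section contradicts the definition without settling it.

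It is also fair that the primary outcome and this one are meant to differ over time. One concerns recurrence within a year; the other is status at a visit. Only disagreement at the same visit is a defect.

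The objection on size stands. A reader might infer that the rule would count most paroxysmal recurrences as successes and push both arms close to 100%. The documents do not support that as a general statement. They give no expected AF burden and no split between paroxysmal and persistent AF, and Study design and participants provides for patients with persistent AF. A patient in AF throughout the visit shows it on both recordings and is not misclassified.

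**Conclusion.** The point holds as an internal contradiction in an endpoint definition. The Secondary outcomes text, read as written, gives the opposite classification from the Table 1 footnote and the statistical section for a patient with AF on Holter and a clean visit ECG, and the schedule makes that combination possible at every visit.

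If the literal rule were applied, the between-group difference would be multiplied by s, given equal s in both arms. The loss is large for low-burden paroxysmal AF and small for persistent AF. The power figures rest on assumed Holter AF rates and assumed values of s; they show the direction and the range and do not predict this trial.

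A reader might also infer that the primary result or the sample size is compromised. Neither is: primary-outcome AF is detected on Holter, AF burden is Holter-based too, and the sample size does not use the sinus-rhythm definition. The point should be corrected, but it concerns one secondary outcome.

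**What to change.** State one rule and use it in the Secondary outcomes text, the Table 1 footnote and the statistical section: sinus rhythm at a visit means no AF longer than 30 s, AFL, sustained VT or VF on the 24-h Holter of that visit. Either of two versions is adequate:

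- Holter alone, which the statistical section already names and which is the smallest change; or
- Holter and 12-lead ECG both clean, in which case the criterion for AF on the 12-lead ECG should be stated as well.

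In both versions a clean 12-lead ECG must not override an abnormal Holter. If the either/or wording was meant for visits with only one recording, say so and state how a missing Holter is handled.

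The cost is about one sentence in each place. Both recordings are already scheduled, so no extra data are needed. The downside is a lower reported sinus-rhythm rate than the either-clean rule would give.

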## Abstract

SGLT-2 inhibitor, traditionally used for glycemic control, has several beneficial effects that can help manage heart failure (HF). SGLT-2 inhibitors reduce the risk of cardiovascular mortality in patients with HF. As atrial fibrillation (AF) is closely associated with HF and diabetes mellitus (DM) is a risk factor for AF, we assume that SGLT-2 inhibitors will also show therapeutic benefits regarding AF, especially for rhythm control. This trial has a multicenter, prospective, open, blinded endpoint design. It is a 1:1 randomized and controlled study. A total of 716 patients who are newly diagnosed of AF and DM within 1 year will be enrolled from 7 tertiary medical centers. The trial is designed to compare the effects of SGLT-2 inhibitors and other oral hypoglycemic agents on atrial rhythm control in patients with AF and DM. The primary outcome is the recurrence of AF within a year (including post-antiarrhythmic drugs (AAD) or ablation). The secondary outcomes are the ablation rate within a year, change in AF burden, size of the left atrium, NT-proBNP, the AF symptom score, and the quality of life. This trial will prospectively evaluate the effect and safety of SGLT-2 inhibitors on AF rhythm control in patients with DM. It will provide an invaluable dataset on rhythm control in AF with DM for future studies and offer novel information to assist in clinical decisions. (BEYOND trial, ClinicalTrials.gov number: NCT05029115. https://clinicaltrials.gov/ct2/show/NCT05029115).

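### The sinus rhythm outcome is compared at baseline and leaves out the month 3 and 9 recordings; a repeated-measures analysis with baseline rhythm as covariate would be more precise at little cost (minor)

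*Protocol article*

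**What the plan says.** Table 1 of the protocol article lists "Sinus rhythm maintenance" as a secondary outcome. Its footnote reads "Defined as the absence of clinically relevant arrhythmia (e.g., AF, AFL, sustained VT, and VF" and gives no period. The text of the same section scores a patient as stable when a standard ECG or a Holter "showed no episode of clinically relevant arrhythmia, including AF, at the time of check-up". The proportion, taken over all participants whether or not they were ablated, "is compared between the two groups at baseline, 6-, and 12-month follow-up visits".

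The section on the statistical plan adds: "AF recurrence rate and ratio of sinus rhythm on 24-h holter EKG will be analyzed using Chi square test". It names no visit, no covariate and no way of combining visits.

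The recordings are more frequent than the comparison. Of AF, the section on the study hypothesis says: "It is checked by 24-h Holter ECG every 3 months". Table 5 marks both the 12-lead ECG and the "24-h Holter ECG" at baseline and at months 3, 6, 9 and 12.

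**The concern.** Two features of this comparison use the data poorly.

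- **Baseline.** A between-group comparison at baseline is made before treatment can act. In a randomised trial any difference there is due to chance. The same measurement could instead explain some of the variation in later rhythm, but an unadjusted chi-square test cannot use it.
- **Visits.** Two of the four scheduled post-baseline recordings do not enter this outcome, and the article gives no reason. AF can come and go, so rhythm on a single day is a noisy reading of a patient's state. More readings per patient reduce that noise without any new recording.

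The label adds a smaller problem. *Maintenance* suggests a period, but the definition is status at the check-up. At stake is the precision and the clear naming of one secondary outcome.

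**Working it through.** **1. Recordings against use**

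| Visit | ECG and Holter in Table 5 | Compared for this outcome |
|---|---|---|
| Baseline | yes | yes |
| Month 3 | yes | no |
| Month 6 | yes | yes |
| Month 9 | yes | no |
| Month 12 | yes | yes |

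Half of the post-baseline recordings (2 of 4) are not used for this outcome. One of its three comparison times is before treatment.

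**2. Inputs for the size of the gain**

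The plan states no figure for this outcome, so there is none to reproduce. From the documents: 358 per arm and 10% loss, so 358 × 0.9 = 322 evaluable per arm. Assumed, because the documents give no values: sinus rhythm in 80% v 72% at every visit, an exchangeable within-patient correlation ρ of 0.3, 0.4 or 0.6, and a two-sided 5% test.

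**3. Variance and power**

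The variance of a patient's mean over k visits, relative to one visit, is (1 + (k − 1)ρ)/k.

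For one visit, the standard error of the difference is √[(0.80 × 0.20 + 0.72 × 0.28)/322] = 0.0335. Then 0.08/0.0335 = 2.39, and power = Φ(2.39 − 1.96) = 0.67. For k visits the standard error is multiplied by the square root of the factor.

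| ρ | Factor, 2 visits | Factor, 4 visits | Variance, 4 v 2 visits | Power, 2 visits | Power, 4 visits |
|---|---|---|---|---|---|
| 0.3 | 0.650 | 0.475 | 27% lower | 0.84 | 0.93 |
| 0.4 | 0.700 | 0.550 | 21% lower | 0.81 | 0.90 |
| 0.6 | 0.800 | 0.700 | 12.5% lower | 0.76 | 0.81 |

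The two-visit column pools months 6 and 12, which the plan does not say it will do. A test at a single visit has power 0.67. Any further gain from adjusting for baseline rhythm is not included, because the documents do not show how strongly it predicts later rhythm.

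**4. Patients whose AF falls only at the omitted visits**

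Assume AF on 20% of recordings and a beta-binomial model.

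| ρ | Clean at 6 and 12 | Clean at all four | AF at 3 or 9, among those clean at 6 and 12 |
|---|---|---|---|
| 0.3 | 0.688 | 0.560 | 1 − 0.560/0.688 = 19% |
| 0.4 | 0.704 | 0.601 | 1 − 0.601/0.704 = 15% |
| 0.6 | 0.736 | 0.674 | 1 − 0.674/0.736 = 8.5% |

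These are patients with AF at either omitted visit. AF at both months 3 and 9 with months 6 and 12 clean occurs in only 1.1–2.0% of all patients under the same model.

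**The case against.** A reader might infer more than the documents support, in three ways.

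- **That the month 3 and 9 data are lost.** They are not. The Abstract states: "The primary outcome is the recurrence of AF within a year". With Holter every 3 months, AF at month 3 or 9 counts there, and it also bears on AF-free survival. Month 3 is a named time point for AF burden as well. The recordings are unused for this one outcome only.
- **That a patient in AF at months 3 and 9 is wrongly counted as maintained.** The text defines status at the check-up, so that patient is correctly in sinus rhythm at months 6 and 12, and is still a recurrence. Only the label is loose. The pattern is also rare under the assumptions above.
- **That a visit-averaged model would measure maintenance.** It would not. It averages status over visits, and freedom from AF over the year already has its own outcome.

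Other objections limit the point.

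- Comparing a secondary measure at chosen visits is a legitimate choice and contradicts nothing in the article. The article requires at least 3 months of antiarrhythmic and hypoglycaemic treatment before recurrence is evaluated, so leaving out month 3 can be defended. Averaging it in changes what is estimated and could dilute a later effect. This objection stands, and it is the reason to keep the month 6 and month 12 contrasts.
- The calculation assumes the same rates, effect and correlation at every visit. Recurrence can lead to ablation, which can change later rhythm. The figures are therefore illustrative.
- The follow-up clock restarts at ablation, so recordings at exactly 3, 6, 9 and 12 months from randomisation are not assured for ablated patients. Visit windows are needed.
- That each visit gets its own chi-square test is an inference, since the statistical section names no visit. An analysis plan that is not shown may specify more. The baseline figures may also be meant descriptively. Even so, the article fixes the visits and an unadjusted test, and the suggestion improves on that.

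**Conclusion.** This is a minor point about efficiency and naming. The baseline comparison cannot show a treatment effect, and baseline rhythm would serve better as a covariate. Using all four scheduled post-baseline visits instead of two would lower the variance by about 13–27%, raising power from 0.76–0.84 to 0.81–0.93. That range rests on the assumed 80% v 72% at every visit and on correlations of 0.3–0.6. At the upper correlation the gain is modest (0.76 to 0.81), and an effect that appears only after month 3 would reduce it further. The primary outcome is unaffected.

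**What to change.** - Drop the between-group comparison at baseline, and use baseline rhythm as a covariate.
- Analyse the scheduled recordings at 3, 6, 9 and 12 months from randomisation in one repeated-measures logistic model: GEE with robust standard errors and terms for arm, visit, arm by visit and baseline rhythm.
- Keep all participants, with or without ablation. Define visit windows counted from randomisation, so that patients whose visits restart at ablation can be placed.
- Report the month 6 and month 12 contrasts from the model, and add the effect averaged over the four visits. State that the average includes early rhythm at month 3.
- Rename the outcome *sinus rhythm at scheduled visits*, and leave freedom from AF over the year to AF-free survival.

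The cost is a change of wording, a visit-window rule and a little more analysis work. Table 5 already schedules the recordings. For ablated patients the windows decide which recordings count at each visit, and some visits may have none.

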As dilatation of the left atrium (LA) is associated with AF in both pathophysiologic and prognostic perspectives, we will use the LA size as a secondary outcome. Left atrial remodeling induces electrical modification, which is associated with AF. LA structural remodeling is characterized by atrial dilatation [24]. An increase in the LA size at baseline is associated with progressive LA enlargement and AF recurrence. Hence, the LA size can be considered a prognostic factor for spontaneous conversion of AF [25]. As an indicator of LA dilatation, the left atrial diameter (anterior–posterior) will be measured by transthoracic echocardiography (TTE) at baseline and 12-month follow-up visit [26]. N-terminal pro-B-type natriuretic peptide (NT-proBNP) is often elevated in AF and is higher in severe AF [27,28]. As it is a significant secondary outcome, we will measure the level of NT-proBNP in blood and compare their values in the two groups at baseline and 12-month follow-up visit.

The symptom score is compared by using the EHRA score. It is measured at baseline, 3-, 6-, 9-, and 12-month of follow-up visits. The ratio of asymptomatic participants will be compared between the two groups. To compare the quality of life between the two groups, EuroQoL five-dimensional instrument (EQ-5D, www.euroqol.org) and SF-12 (a shortened version of SF-36, www.sf-36.org) Health Survey will be used, and assessments will be conducted between the data on baseline and 12-month follow-up visit.

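### The EHRA symptom score is compared only as the proportion asymptomatic, without the baseline class, which costs sensitivity on one secondary outcome (minor)

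*Protocol article*

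**What the plan says.** Table 1 of the protocol article names the outcome as a score: "Symptom score (EHRA score)". The Secondary outcomes text gives the instrument, "The symptom score is compared by using the EHRA score", and the schedule: "It is measured at baseline, 3-, 6-, 9-, and 12-month of follow-up visits". Table 5 confirms that it is collected at all five visits. The comparison then described is "The ratio of asymptomatic participants will be compared between the two groups". No visit is named for it, and the baseline class has no stated part in it.

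The section on the statistical plan assigns tests to other outcomes, for example "AF recurrence rate and ratio of sinus rhythm on 24-h holter EKG will be analyzed using Chi square test", but none to EHRA.

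On entry, Table 3 asks for "At least one episode of AF* that is documented during the prior year by any kind of ECG recording". Neither Table 3 nor Table 4 contains a symptom criterion. For the Division of Endocrinology, Study design and participants says that "every patient newly diagnosed with DM during the enrollment period will be asked for 12-lead ECG and 24-h Holter ECG", and that "those with AF > 10 s in 12-lead ECG or >30 s in 24-h Holter ECG can be recruited for the trial".

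**The concern.** The state being compared, freedom from symptoms, is one that patients may already be in when they are randomised. Screening patients who came for diabetes makes this more likely than recruiting people who sought care for palpitations.

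Two losses follow. First, a patient asymptomatic at entry who stays so adds to the favourable count in both arms and carries little information about treatment. Second, a patient who moves from a severe to a milder symptomatic class is recorded the same as one who did not change. Both shrink the observable difference while the baseline value that could recover some of it is already being collected. At stake is how well the trial can detect a symptom benefit on this outcome, and how the reported percentage can be read: it describes a state at follow-up, not improvement from entry.

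**Working it through.** **Inputs.** From the document: 358 patients per arm and 10% loss, so 358 × 0.9 = 322 evaluable per arm; alpha 5%, taken as two-sided. The article states no power, effect or distribution for EHRA, so there is no EHRA figure to reproduce. The total of 716 was sized on AF recurrence and does not bear on this point. EHRA is treated below as four ordered classes, class I meaning no symptoms. All other inputs are assumptions.

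**1. Validity.** With equal rates in both arms and 30% or 50% asymptomatic at entry, the simulated type I error over 20,000 trials is 0.0497 and 0.0494. There is no bias between the arms.

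**2. Dilution.** Let b be the share asymptomatic at entry. Assume that 90% of these remain so in both arms, and that 40% (control) or 52% (treated) of symptomatic patients become asymptomatic. Then

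pC = 0.90b + 0.40(1 − b), pT = 0.90b + 0.52(1 − b), difference = 0.12(1 − b).

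Power = Φ{[difference − 1.96·√(2p̄(1 − p̄)/n)] / √[(pC(1 − pC) + pT(1 − pT))/n]}, with n = 322 and p̄ the mean of pC and pT.

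For b = 0.3: pC = 0.550, pT = 0.634, difference 0.084, p̄ = 0.592. The two square roots are 0.0387 and 0.0386, so power = Φ[(0.084 − 0.0759)/0.0386] = Φ(0.21) = 58%.

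| Asymptomatic at entry | pC | pT | Power, all patients | Power, symptomatic at entry only |
|---|---|---|---|---|
| 0% | 0.400 | 0.520 | 87% | 87% |
| 20% | 0.500 | 0.596 | 69% | 78% |
| 30% | 0.550 | 0.634 | 58% | 73% |
| 40% | 0.600 | 0.672 | 48% | 66% |
| 60% | 0.700 | 0.748 | 28% | 49% |

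The last column uses 322(1 − b) patients per arm. Dropping the patients asymptomatic at entry raises power even though the sample is smaller.

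**3. Collapsing the classes.** With a common odds ratio of 1.5 and 322 per arm, a Wilcoxon test on the four classes has 80% power against 68% for the class I proportion when 30% of controls are in class I. The figures are 78% against 72% at 40%, 75% against 72% at 50%, and 70% against 69% at 60%. The gain fades as more controls are asymptomatic. At the other extreme, suppose all improvement lies among symptomatic classes (control 40/20/30/10%, treated 40/35/20/5%). The proportion then has only its 5% alpha, and Wilcoxon about 60%.

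**4. Both losses together, with baseline adjustment.** Latent-normal model: 20-40% asymptomatic at entry, the rest split 50/40/10 over the other classes, baseline to follow-up correlation 0.4-0.6, treatment shift 0.2 SD.

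- *No average change in either arm.* Under no treatment effect, 38-65% of controls asymptomatic at follow-up were so at entry, and 39-61% of patients who improve by at least one class are not counted. With the shift, power is about 47-58% for the proportion and 69-80% for a proportional-odds model adjusted for baseline class. Repeat runs gave 46-57% and 63-84%.
- *Both arms improve by 0.5-0.8 SD, with 60-71% of controls in class I at follow-up.* Power is 45-56% for the proportion, 46-59% for an unadjusted rank test and 50-66% for the adjusted ordinal model. Improvers not counted fall to 21-32%.

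The adjusted model did better in every setting: by about 16-29 points with no common improvement, and by about 8-23 points with a common improvement of 0.6-0.7 SD. These runs are small. At 200 runs the standard error near 50% power is √(0.5 × 0.5/200) = 3.5 points, so only the rounded ranges should be relied on.

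**The case against.** The strongest objection concerns size. Every participant receives an anti-arrhythmic drug, with cardioversion for persistent AF and step-up to ablation on recurrence, so both arms should improve. When they do, the gain from the ordinal scale alone falls to 1-4 points and most of what is left comes from baseline adjustment. This stands, and the conclusion is sized accordingly.

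A second objection is that adjustment, model and visit are usually left to a SAP, that the statistical section names no test for EHRA, and that the sentence on the EHRA score leaves room for the full scale. In part this stands: a missing test or visit is no fault here. But the article does choose a comparison, and that comparison ignores most of a graded score, so proposing a better one is not a complaint about missing detail.

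Third, freedom from symptoms is easy to read and matches a decision point in the trial, since symptomatic recurrence prompts consideration of ablation. That is a good reason to keep reporting it.

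A reader might also infer that patients asymptomatic at entry are counted as treatment successes, and partial improvers as failures. The document does not support this. It defines no responder, success or improvement endpoint; it compares a state between randomised groups. Nor is remaining asymptomatic empty of information: such a patient can develop symptoms if AF recurs, and counts favourably only if still free of them at follow-up.

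**Conclusion.** The point holds as a loss of efficiency on one secondary outcome; severity is minor. Under the assumptions shown (322 per arm, 0.2 SD latent shift), power is roughly 40-60% for the stated proportion. For the baseline-adjusted ordinal model it is about 65-80% without common improvement and about 50-70% with a common improvement of 0.5-0.8 SD. The direction was the same in every setting tried. The size depends on the entry distribution, the correlation and the average improvement, none of which the article gives.

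Two stronger readings should be resisted. The comparison is not invalid: randomisation balances entry status in expectation, and type I error stays near 5%. Nor can one say that a real symptom benefit will probably be missed because of this choice: power for the proportion is near one half under these assumptions, and the better model would also miss such an effect fairly often.

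**What to change.** In Secondary outcomes, replace the sentence on the asymptomatic ratio with: *EHRA class at the 12-month visit will be compared between the randomised groups by a proportional-odds model adjusted for baseline EHRA class; the proportion asymptomatic at that visit will be reported alongside it, overall and by baseline class.* Because the follow-up clock restarts at ablation for patients who step up, the sentence should also say from which starting point the 12 months are counted.

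The cost is one sentence and no new data, since EHRA is already recorded at baseline and at every visit. The small downside is that a common odds ratio is harder to explain than a percentage. Reporting the percentage as well covers this, and the breakdown by baseline class shows how much of it reflects entry status.
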